### Sample size calculation

The sample size was calculated using the GRANMO v.7.12 (IMIM, Barcelona) programme. Considering an alpha risk of 0.05 and a beta risk of less than 0.2 in a bilateral contrast, it was necessary to include 72 patients in each group (intervention and control) to detect a difference equal to or greater than 1% of HbA1c [5] between the two groups. A common standard deviation of 1.46 [6] and a loss rate to follow up of 20% were assumed.

Considering that each physician/nurse that makes up the Basic Care Unit will coordinate their diabetic patients, a correction may be made due to a possible contamination in the analysis between individuals by assigning each Primary Care Team to intervention or control groups and taking into account the design effect. According to a study performed by our research group [16], we estimated that each GP would have 15 potential candidate patients with HbA1c > 9%. Assuming that the intra-class correlation coefficient for Primary Care is 0.05 [29], resulting in a 1.7 design effect, the required sample size will be 42 * 1.7 = 72 individuals in each group.

Each control or intervention group consists of 3 basic health areas, one in each geographical area, each with a mean of 10 BCUs and 15 individuals per basic care unit. Thus, the sample finally calculated to obtain statistical significance was 72 subjects per centre, leading to a total of 648 study subjects.

First patient enrolled in the study INTEGRA on 09/12/2015.

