### Statistical analysis plan

For data analysis, the IG-1, the IG-2, and the control group will be compared. All analyses will be carried out using bilateral tests with a nominal significance level of 0.05. However, if the comparisons obtain a *p*-value of less than 0.10, they will also be discussed as indicative of trends. Initially, basal characteristics of all groups will be evaluated to establish homogeneity in age, socio-demographic, comorbidities, laboratory parameters, concomitant medication and diabetes complications. An initial, descriptive comparison between groups of all variables will be performed to evaluate their baseline balance. Statistical significance will be assessed by the chi-square or t-test between the groups. Exploratory analyses will be applied when necessary.

The main variable is set as the difference in mean HbA1c values between the final visit and baseline. The difference will be evaluated in terms of the evolution of HbA1c as contrasted between groups by paired t-Student, or if the assumption of normality is not met for the right non-parametric.

If differences in the characteristics of the patients in each group are observed in the descriptive section of the study, a linear regression of the main variable (parameter evolution during the study) will be adjusted. This linear regression adjusted for the variables identified in the descriptive section, or the ability to adjust the model by setting a propensity score, will be evaluated. For all models, the distribution of waste will be studied, as well as the coefficient of determination (R2), to check for the correct setting.

As was done in Vinagre et al. [4], a subgroup analysis will be performed by a) gender (male / female), b) age: < age 65 / ≥ 65, and c) according to HbA1c control levels (< 10% / ≥ 10%).

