We will determine the prevalence of patients who achieved a concentration of HbA1c of less than 7% at the end of the study. A categorical variable (No, Yes) will be calculated. The analysis of a significant decrease in HbA1c will be carried out using a logistic regression analysis adjusting by the effect of the study groups (as *dummy* variable) and the main factors previously determined to be associated with the target of 7% (in a previous descriptive analysis or adjustment by the *propensity score*). The power of discrimination (C statistic and ROC curve) and calibration (Hosmer & Lemeshow test) for the final models will be studied. The software we will use for analysis of the data will be R Core Team (2014). R: A language and environment for statistical computing. R Foundation for Statistical Computing, Vienna, Austria (http://www.R-project.org/).

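### The sample size allows for clustering by care unit, but the named tests do not: for IG-1 versus IG-2 a nominal 5% test has a true error of about 13% at the protocol's own design effect of 1.7

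*Protocol article*

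**What the plan says.** The Sample size calculation section of the protocol article treats the study as clustered. It describes "assigning each Primary Care Team to intervention or control groups and taking into account the design effect", takes an ICC of 0.05 with 15 candidate patients per GP, and multiplies 42 patients by a design effect of 1.7 to reach 72. It adds: "Each control or intervention group consists of 3 basic health areas, one in each geographical area". Each area has a mean of 10 basic care units. The plan is 72 subjects per centre and 648 in total. The Study design section explains that treatment cannot sensibly differ between patients of the same professional in one centre.

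The Statistical analysis plan section sets the level: "All analyses will be carried out using bilateral tests with a nominal significance level of 0.05". It names these between-group methods:
- a t-test on HbA1c change, or a non-parametric alternative;
- if baseline characteristics differ, "a linear regression of the main variable (parameter evolution during the study) will be adjusted", with covariates from the descriptive comparison or a propensity score;
- for HbA1c below 7%, a "logistic regression analysis adjusting by the effect of the study groups", entered as dummy variables, plus associated factors.

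No method includes centre, team or care unit. The nearest wording, in the sample size section, is that a correction may be made, and it leads only to a larger sample.

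**The concern.** The sample size and the analysis rest on different assumptions about the same data. If outcomes of patients who share a professional or centre are correlated, a test that treats patients as independent understates the variance of the group difference. Enlarging the sample protects power. It does not protect the type I error, which depends on the variance estimate used in the test. Patient-level covariates or a propensity score do not in general remove this correlation.

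The Study design section makes IG-2 the comparator for IG-1, the main intervention. That contrast sets three centres against three. With the named tests, ordinary differences between centres or care units would be read as an effect of the monographic consultation more often than 5% of the time. Confidence intervals for HbA1c, lipids, blood pressure and target attainment would be too narrow.

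**Working it through.** **Inputs from the Sample size calculation section**
- Error rates: "Considering an alpha risk of 0.05 and a beta risk of less than 0.2 in a bilateral contrast".
- Difference: 1% HbA1c.
- Spread and loss: "A common standard deviation of 1.46 [6] and a loss rate to follow up of 20% were assumed".
- ICC 0.05; 15 patients per GP; 10 care units per centre; 3 centres per group; 72 patients per centre.

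**The plan's own figures reproduce**
- n per group = 2 × [1.46 × (1.96 + 0.842)]² / 1² = 33.46.
- After 20% loss: 33.46 / 0.8 = 41.8, so 42.
- Design effect = 1 + (15 − 1) × 0.05 = 1.70.
- 42 × 1.7 = 71.4, so 72; 72 × 9 centres = 648.

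**Cluster sizes implied by 72 per centre**
- Completers per centre: 72 × 0.8 = 57.6, about 58.
- Recruited per care unit: 72 / 10 = 7.2. Completers per care unit: 57.6 / 10 = 5.76.

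**True error of an independent-patient test, IG-1 versus IG-2**

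With DE = 1 + (m − 1) × ICC, the true two-sided error is 2 × [1 − Φ(1.96 / √DE)].

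| Level at which the ICC acts | ICC | m | DE | 1.96/√DE | True error |
|---|---|---|---|---|---|
| Care unit, completers | 0.05 | 5.76 | 1.24 | 1.76 | 7.8% |
| Care unit, recruited | 0.05 | 7.2 | 1.31 | 1.71 | 8.7% |
| Protocol's own design effect | 0.05 | 15 | 1.70 | 1.50 | 13.3% |
| Centre, completers | 0.05 | 57.6 | 3.83 | 1.00 | 31.7% |
| Care unit, completers (assumed ICC) | 0.01 | 5.76 | 1.05 | 1.91 | 5.6% |
| Centre, completers (assumed ICC) | 0.01 | 57.6 | 1.57 | 1.57 | 11.7% |

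A simulation of the ordinary two-sample t-test (20,000 runs per case, ICC 0.05) gave 7.8% with 6 per unit, 8.5% with 7, 13.4% with 15, and 32.1% with 3 centres of 58 per group.

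**Intervention versus SIDIAP controls**

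Assume that the controls are spread over so many centres that they are nearly independent. The variance inflation is then the average of DE and 1. At ICC 0.05:
- m = 5.76: (1.238 + 1) / 2 = 1.119, error 6.4%;
- m = 15: (1.70 + 1) / 2 = 1.35, error 9.2%;
- m = 57.6: (3.83 + 1) / 2 = 2.415, error 20.7%.

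**Power of a centre-level analysis, IG-1 versus IG-2**

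The variance of a centre mean is 1.46² × [ICC + (1 − ICC)/58]. The standard error of the difference is √(2 × variance / 3). Power for a 1% difference uses the noncentral t distribution with 4 degrees of freedom.
- Centre ICC 0.05: SE 0.307, power about 69%.
- Centre ICC 0.02: SE 0.229, power about 90%.
- Centre ICC 0.01: SE 0.196, power about 96%.

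With district as a fixed effect, 2 degrees of freedom remain. If district absorbs no variance, power at ICC 0.05 is about 43%.

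**The case against.** The strongest reply concerns size and scope.

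- **Level of the ICC.** The protocol applies 0.05 per GP, not per centre, so the figure of about 32% moves that ICC to a level the document never states. This stands, and 13% is the figure tied to the protocol's own inputs. A reader might go further and quote 36%, which needs 72 analysed patients per centre. That number already allows for 20% loss, so the documents do not support it as the analysed size.
- **Value of the ICC.** The 0.05 is described as a value for primary care, not for HbA1c change, and the true value may be lower. This stands, and it is why the ICC 0.01 rows are shown.
- **District matching.** Each group has one area per district, and areas are chosen to be similar. Between-district variance then cancels in the IG-1 versus IG-2 difference, so the centre-level figure is nearer an upper case than an expected value.
- **Controls.** A reader might apply the IG-1 versus IG-2 figures to every comparison. The Control group section samples individual patients from SIDIAP, and the Study design section takes them from non-participating centres. The sample size section instead gives the control group three areas. The two descriptions do not fit together, and under the first the inflation is smaller.
- **Condensed article and exploratory label.** The article may shorten a fuller plan, and the Abstract calls phase 2 exploratory. But this section names the tests and goes down to R², the C statistic and the calibration test. The objection is to the methods stated, not to missing detail. The exploratory label does not make a 5% level hold.

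**Conclusion.** The point holds. The sample size assumes within-cluster correlation, and the named tests assume none. Followed as written, they give standard errors that are too small.

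For IG-1 versus IG-2, the best-anchored estimate of the true error is about 13% against a nominal 5%. It is about 8–9% at the care-unit sizes that recruitment implies. About 32% is an upper case that needs the ICC of 0.05 to act between centres. An assumed ICC of 0.01 gives about 6–12%. Against SIDIAP controls the range at ICC 0.05 is about 6–21%, provided those controls are nearly independent. Every case computed exceeds 5%, but the size depends on the value and level of the ICC, which the document does not settle.

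These figures cover clustering alone. A reader might infer that a cluster term would make the comparison sound. It would not: assignment is non-randomized, and with three centres per group confounding by centre remains.

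**What to change.** Amend the Statistical analysis plan section to:
- state that between-group analyses of HbA1c, continuous secondary outcomes and target attainment account for clustering. Use a mixed model with centre effects, care-unit effects where identifiers are available, and small-sample degrees of freedom; or use a centre-level analysis for IG-1 versus IG-2;
- remove the patient-level t-test as the inferential test;
- report the observed ICC;
- confirm whether centre or care-unit identifiers can be extracted for the SIDIAP controls. The records are anonymised and the article does not say. Reconcile the two descriptions of how that group is formed;
- say that the adjustment does not deal with confounding by centre.

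Recruitment and treatment do not change. The cost is wider intervals and lower power: for IG-1 versus IG-2 on 4 degrees of freedom, about 69%, 90% and 96% at centre ICC 0.05, 0.02 and 0.01, against the planned 80%. Power is lower still if district is a fixed effect that absorbs little variance, so that choice should be made in advance and stated with its power.

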### Characteristics of participants

The inclusion criteria include the following: T2DM of more than one year of disease duration, age between 30 and 80 years, HbA1c > 9% in the last test performed in the 12 months prior to study inclusion, with no change in antidiabetic treatment within the previous 3 months. The changes in the dose of a drug in the antidiabetic treatment will be not considered as exclusion criteria.

The exclusion criteria include the following: T2DM controlled by endocrinologist at the moment of inclusion, systemic glucocorticoid treatment (ATC code: H02AB) or orlistat treatment (ATC code: A08AB01) (chronic or during the two months prior to inclusion), estimated life expectancy < 2 years, active treatment for malignancy (other than basal cell cancer or squamous cell skin cancer), serious mental disorders (psychosis, bipolar affective disorder, severe depressive episode with psychotic symptoms), class III or IV (New York Heart Association functional classification) heart failure (ICD-10: I50), dementia, renal transplantation or current dialysis treatment, history of drug and/or alcohol abuse (ICD-10: F10-F14), pregnancy or lactation, treatment with immunosuppressive drugs, haemoglobinopathies (ICD-10: D58.2), or chronic anaemia, body mass index (BMI) > 45 kg/m^2^, or any conditions that the investigator considered could prevent the patient from completing the study.

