## Discussion

According to the SIDIAP database, which contains all the data entered into the eCAP, the database used in Catalan Health Institute, 79.6% of the patients have HbA1c values ≤8%, and the proportion of patients with fair control (HbA1c ≤7%) is 56.1% [4].

The INTEGRA study defines potential pragmatic new strategies to improve metabolic control in patients with very poorly controlled T2DM in the primary care setting that, if demonstrated to be effective, could be implemented by professionals in their real-life practices at ICS. The research team agreed to define poorly controlled T2DM patients as those who had HbA1c levels ≥9%. This is because at the time of the protocol writing, local and international guidelines were recommending the initiation of insulin therapy in type 2 diabetes when HbA1c levels were between 8.5 and 10% [32, 33]. Due to this the lack of agreement, the ≥9% cut-off was chosen in accordance with the AACE Comprehensive Diabetes Management Algorithm 2013 [34], which is actually a value in between all recommendations. Moreover, our population characteristics and primary health care patterns of treatment were taken in account. Indeed, those subjects with HbA1c levels > 9% are usually the ones that most often need to be treated with insulin, but this therapy is frequently delayed or not even started by some general practitioners in our primary health-care centres [4]. Some studies report that a multifactorial target intervention used for the management of T2DM is effective and feasible in clinical practice. An intensive intervention strategy delivered at the clinical level is associated with a significant and durable improvement in HbA1c and major cardiovascular risk factors, well beyond that achieved with the usual practices [35]. Some studies describe that patient-centred care is more valuable when targeted to patients with HbA_1c_ > 8.5%. Patient-centred care was most effective and cost-effective in those patients, resulting in more improved glycaemic and metabolic control but also improving quality-adjusted life years and costs of associated complications [36].

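### Effect modification by age and HbA1c is examined only through splits at 65 years and 10%; if modification is roughly linear, this discards about a third or more of the information

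*Protocol article*

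**What the plan says.** The Statistical analysis plan section of the protocol article announces that "a subgroup analysis will be performed by a) gender (male / female") and continues with "b) age: < age 65 / ≥ 65, and c) according to HbA1c control levels (< 10% / ≥ 10" (per cent). The reason given is that an earlier study did the same. The time of the HbA1c measurement is not stated; I read it as baseline.

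The same section describes two regressions, and neither addresses who benefits. The linear model for HbA1c change is adjusted for patient characteristics only if the groups are found to differ on them. The logistic model for reaching 7% adjusts for factors associated with that target. No group-by-covariate term appears in either.

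Eligibility (Characteristics of participants) is "age between 30 and 80 years" and "HbA1c > 9% in the last test performed in the 12 months prior to study inclusion". Table 1 shows that age and HbA1c are collected in both intervention groups and, from SIDIAP, in the control group.

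**The concern.** Both variables are available as measured values in all three groups, yet the stated analysis reduces each to two levels. The HbA1c cut suits this population poorly. The lower stratum runs only from 9% to 10%, and the upper stratum has no ceiling. Patients at 9.9% and 10.1% count as different, while patients at 10.1% and 13% count as the same.

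The Background argues for directing interventions at patients with poorer control, so whether benefit varies with starting HbA1c is a natural question for readers of the results. At stake is the chance of showing such variation, or of estimating it precisely enough to rule out a large one. The loss comes from the cut-points themselves and is separate from how many subgroups are tested.

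**Working it through.** **The plan's own figures.** The plan gives no precision or power for the subgroups. Its sample size reproduces and is used here only for scale. With 1.46 as SD and 1 point as difference, 2 × (1.46 × 2.80)² ≈ 33.5 per group; 33.5 / 0.8 ≈ 42; 42 × 1.7 = 71.4, rounded up to 72; 72 × 9 = 648, or 216 per group.

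**Formula.** For a linear group-by-covariate interaction, the share of information kept when a covariate X is replaced by an indicator I(X ≥ c) is the squared correlation between X and I. If the continuous test has 80% power at two-sided 0.05 (the plan's level: "All analyses will be carried out using bilateral tests with a nominal significance level of 0.05"), the power after the split is Φ(2.80 × √share − 1.96).

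**Benchmark.** For a normal covariate the share is φ(z)² / [p(1 − p)], with p the fraction above the cut and z the matching normal quantile. At the median this is 2/π = 63.7%, a loss of 36.3%. The loss rises to 37.8% at a 40/60 split, 42.4% at 30/70 and 51.0% at 20/80.

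**HbA1c, central assumption.** The Discussion says of SIDIAP patients that "79.6% of the patients have HbA1c values ≤8%, and the proportion of patients with fair control (HbA1c ≤7%) is 56.1" per cent. A lognormal through those two points has log-scale SD (ln 8 − ln 7) / (0.827 − 0.154) = 0.198 and median 6.79%. Restricted to values above 9%:
- share of patients at 10% or more: 0.0254 / 0.0775 = 33%
- information kept: 63%
- power: Φ(2.80 × √0.63 − 1.96) = 60%

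**Age, central assumption.** Normal with mean 63 and SD 10, truncated to 30–80 (the mean and SD are assumed):
- share of patients at 65 or more: 39%
- information kept: 62%
- power: 60%

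**Range over other assumptions.**

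| Covariate and assumed distribution | Information lost |
|---|---|
| Age, truncated normal on 30–80, mean 55–68, SD 9–13 | 33% to 60% |
| Age, uniform on 30–80 | 37% |
| HbA1c, normal through the same two SIDIAP points, above 9% | 34% |
| HbA1c, other truncated normals above 9% | 33% to 54% |
| HbA1c, exponential excess over 9%, mean 0.75 to 2 points | 36% to 62% |

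For the exponential with mean excess m, the share kept is (1/m)² × p/(1 − p) with p = exp(−1/m). At m = 2 this is 0.25 × 0.607 / 0.393 = 38.5%, a loss of about 62%. Capping HbA1c at 16% reduces that loss to 51%.

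The range is not a mathematical bound. A younger, narrower age distribution (mean 55, SD 8) loses 65%. A flat distribution cut exactly at its middle loses 25%, but a flat HbA1c distribution symmetric about 10% is hard to reconcile with entry at above 9%.

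**Scale.** With 20% loss and design effect 1.7, each group carries 216 × 0.8 / 1.7 ≈ 102 effective patients. Taking 1.46 as the residual SD, a continuous interaction between two groups has 80% power for a slope of 2.80 × 1.46 × √(2/102) / SD of baseline HbA1c. That is about 0.57 HbA1c points per baseline point if that SD is 1.0, and about 0.38 if it is 1.5. The split needs a between-stratum difference of about 1.15 points at 50/50 and 1.2 points at 33/67.

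**The case against.** Pre-specified clinical categories are common and guard against data-driven cut-points, and the plan contradicts nothing by using them. A full analysis plan may exist, and the article allows for unspecified exploratory analyses. No stated aim concerns effect modification. The scale figures also show that either analysis is weak for modest modification in a trial planned "to detect a difference equal to or greater than 1% of HbA1c" overall. All of this stands. It keeps the point small and is a reason to retain the table. It does not remove the point, because the section does fix how age and HbA1c are to be examined.

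A reader might infer three stronger things that the documents do not support:
- **That more than a third of the information is lost whatever the truth.** The sample distributions are not given, some favourable age distributions lose only 33%, and the calculation presumes a roughly linear gradient. If benefit stepped exactly at 65 years or 10%, the split would lose nothing and a linear term would be the inefficient choice.
- **That the Background asserts a gradient above 9%.** It reports larger improvements at high baseline values, especially over 8%, and every eligible patient is already above that.
- **That the remedy only adds two terms to a model already planned.** The planned linear regression depends on finding baseline imbalance, and three groups with two modifiers need four interaction coefficients.

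**Conclusion.** The point holds as a cheap improvement. The only stated analysis of effect modification by age and HbA1c uses two-category splits, and the HbA1c cut leaves a one-point band below it. If modification is roughly linear, about a third or more of the information is discarded: 33% to 62% over the assumed distributions, and 37–38% under the central ones. In the central case 80% power becomes about 60%, equivalent to needing about 1.6 times as many patients (1/0.63). These figures rest on assumed distributions and on linearity, neither of which the documents supply. The analysis is secondary, and a reader should not conclude that the primary HbA1c comparison is affected.

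**What to change.** Keep the 65-year and 10% subgroup table for description. Assess modification in a linear model for HbA1c change that is fitted regardless of baseline imbalance. Include group, baseline HbA1c and age as main effects, plus group-by-baseline-HbA1c and group-by-age interactions with both covariates continuous. Check linearity with a spline, and show the estimated group difference with its confidence interval across the observed range of each covariate. State that the HbA1c value used is the baseline one.

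The cost is one additional secondary model with four interaction coefficients (two group contrasts × two modifiers), and more if a spline is retained. The downside is the linearity assumption, which the spline check addresses in part. No new data, visits or patients are needed.
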